### 3.3. Instruments of Measurement

#### 3.3.1. Tests and Questionnaires

In this subsection, we present tests and questionnaires to determine the basic state of each participant or those to be used before and after the intervention with the participants. It is important to know the quality of life and emotional situation of the subjects to be measured, with the aim of subsequently contrasting the physiological measurements taken. There are two populations: children and adults. In addition, the cognitive status of the subjects may vary. All of these are factors to be taken into account when applying the measurement instruments. Sometimes, depending on the abilities of individual participants that may prevent them from completing the questionnaires independently, their family members or the professionals of the centers will be responsible for completing the questionnaires.

ICF for the adult population [29].MACS [31] for children.GMFCS [30] for children.CFCS [33] for children.KIDSCREEN Questionnaire (accessed on: https://www.kidscreen.org/english/questionnaires/, accessed on 10 May 2024): Will be used in its 10-item version for the evaluation of the child population; it is an instrument that measures the quality of life related to health.Musical Preferences Questionnaire: This measure will ask about songs that motivate the subjects and generate a positive and active emotion. Music serves as a catalyst to enhance the enjoyment of the activity. Hence, understanding the musical preferences of the individual user is crucial. The objective is not to employ a uniform, neutral piece of music for all participants and examine its isolated impact.EVEA scale and free text to be filled in by caregivers or relatives. The EVEA scale, according to [26], is consistent and has the ability to detect changes in mood. This scale will be used at the beginning of the data recording once the sensors have been placed and at the end of recording time.

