Even though every session has a unique theme, the format of the sessions will remain consistent. The sensors will initially be placed on the participant and a data acquisition test will be performed to ensure that all data are being captured correctly. Data recording will initiate while the user is responding to the EVEA test; this phase will be used as a baseline for the session—note that a minimum of two minutes is required. The following phase will be the main activity, with a 15 min time limit, ending with a final EVEA test with identical specifications to the initial one, which will be used as the final baseline. Both baselines allow for the detection of the measurement differentials in each session, alongside the analysis of the participant’s progression during the activity. Each participant is expected to finish the protocol within two weeks, where the first and second sessions will be scheduled for the first week, and the third and fourth sessions will be set for the second one. Figure 4 shows a diagram of the described protocol.

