### 4.2. Data Analysis

In general, numerical variables will be expressed as mean (M) and standard deviation (SD), including range, minimum and maximum.

For the first part of the study, we will compare the dependent variables obtained between sessions 1 and 2 for each subject using the permutation test of the difference in means between different data windows. Those dependent physiological variables that mark significant differences for most of the subjects will be chosen. Changes in EVEA test responses between sessions 1 and 2 will serve as reinforcement for detecting the level of emotional change.

We will also correlate the results of the EVEA test with the base state questionnaires to determine the existence of some type of dependency between the base level of EVEA and its variation with respect to the base state. This dependence will be explored with the Spearman or Pearson correlation test.

For the second part, first, we will analyze the variation in EVEA for sessions 3 and 4 to determine if there is a significant dependence on the independent variable (music) between stages A and B for all the participants. We will use the Kruskal–Wallis test, which does not require any type of assumption regarding the normality and homoscedasticity of the samples. These variations will also be correlated with the quality of life scale (ICF, GMFCS, MACS, CFCS, or KIDSCREEN), as was carried out with the data from the first part.

For the physiological variables and the average kinetic energy, we will determine if their variations are significant between A and B by means of a Kruskal–Wallis test applied to the group of subjects, but also at the individual level by means of a permutation test.

The significance of the tests will be set at three levels, indicated with * (*p* < 0.05), ** (*p* < 0.01) and *** (*p* < 0.001).

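### Section 4.2 names two different pairs for the Part 1 EVEA correlation; one of them, base level against its own change, is biased negative by measurement error alone

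*Protocol article*

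**What the plan says.** Section 4.2, on the first part of the study, opens the relevant sentence with the operands: "We will also correlate the results of the EVEA test with the base state questionnaires". The same sentence then gives the purpose, which is to find a "dependency between the base level of EVEA and its variation with respect to the base state". The next sentence fixes the method: "This dependence will be explored with the Spearman or Pearson correlation test".

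Section 3.3.1 gives the timing of EVEA: "This scale will be used at the beginning of the data recording once the sensors have been placed and at the end of recording time". Section 3.3.3 confirms that the same instrument is used twice in a session, "ending with a final EVEA test with identical specifications to the initial one", and adds: "Both baselines allow for the detection of the measurement differentials in each session".

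For the second part, Section 4.2 says of the EVEA variations in sessions 3 and 4: "These variations will also be correlated with the quality of life scale". It lists ICF, GMFCS, MACS, CFCS or KIDSCREEN and says that this follows what was done with the first-part data.

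On significance: "The significance of the tests will be set at three levels", namely 0.05, 0.01 and 0.001, with no test exempted.

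**The concern.** The opening of the sentence pairs EVEA with external questionnaires. Its end pairs the base level of EVEA with the variation of EVEA, and the method sentence refers back to that second pair. An analyst who follows the wording to the letter could correlate initial EVEA with final minus initial EVEA and test the result against zero.

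That test is mathematically coupled. Any error or momentary fluctuation in the initial score enters one variable with a plus sign and the other with a minus sign. The expected correlation is then negative even when true change has nothing to do with true starting mood. The likely product would be a starred negative correlation, read as participants with a worse starting mood improving more, when regression to the mean had produced it.

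**Working it through.** **Inputs from the protocol article.** The Cochran sample size is 36 (Section 4.1) and the planned enrolment is 40 (Section 3.2). The lowest threshold is p < 0.05 (Section 4.2); sidedness is not stated, so two-sided is assumed. EVEA is taken at the start and end of each session (Sections 3.3.1 and 3.3.3).

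**The plan's own figure.** n0 = 1.96² × 0.25 / 0.15² = 42.68. With a population of 200, n = 42.68 / (1 + 41.68/200) = 35.32, rounded up to 36. It reproduces, and is used here only as a sample size.

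**Assumptions.** The documents give neither a reliability nor an SD for EVEA, so both are shown as ranges. Let initial X = T + e1 and final Y = T + D + e2, with observed initial variance 1, reliability R, and true change D (SD s, in baseline-SD units) independent of true mood T. Taking variation as Y − X is an inference from the two EVEA administrations per session; Section 4.2 does not define it.

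**Expected correlation when there is no true dependence.**

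corr(X, Y − X) = −(1 − R) / √(2(1 − R) + s²), which reduces to −√((1 − R)/2) when s = 0.

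For example, R = 0.8 and s = 0 gives −0.2/√0.4 = −0.32. R = 0.8 and s = 0.5 gives −0.2/√0.65 = −0.25. R = 0.9 and s = 1 gives −0.1/√1.2 = −0.09.

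**Rejection rate at nominal 5%, n = 36** (20,000 simulated normal samples per case):

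| R | s | expected r | Pearson | Spearman |
|---|---|---|---|---|
| 0.5 | 0 | −0.50 | 89% | 85% |
| 0.7 | 0 | −0.39 | 67% | 61% |
| 0.8 | 0 | −0.32 | 48% | 43% |
| 0.9 | 0 | −0.22 | 26% | 24% |
| 0.5 | 0.5 | −0.45 | 80% | 75% |
| 0.7 | 0.5 | −0.33 | 49% | 45% |
| 0.8 | 0.5 | −0.25 | 31% | 29% |
| 0.9 | 0.5 | −0.15 | 14% | 13% |
| 0.9 | 1 | −0.09 | 8% | 8% |
| 1.0 | 0.5 | 0 | 5% | 5% |

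With 40 subjects and s = 0, the Pearson rates are 92%, 71%, 52% and 29% for R = 0.5, 0.7, 0.8 and 0.9. Spearman does not remove the problem.

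**The other pair.** EVEA change against an external questionnaire that is unrelated to the change rejects in about 5% of samples, including when the questionnaire is correlated with true mood.

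**Two common substitutes.** Correlating change with the mean of the two scores gives about 5% when s = 0. When true change varies, it raises the final variance to 1 + s², and

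corr(Y − X, (X + Y)/2) = (s²/2) / √{(2(1 − R) + s²) × (2 + s² + 2R)/4}.

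R = 0.8, s = 0.5 gives 0.125/√(0.65 × 0.9625) = 0.16. R = 0.9, s = 1 gives 0.5/√(1.2 × 1.2) = 0.42. The rejection rates at n = 36 are 15% and 74%; at R = 0.8, s = 1 the rate is about 67%. Comparing initial and final variances fails for the same reason.

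**The case against.** The strongest reply is that the coupled test is probably not what the authors intend. The main clause names EVEA results and questionnaires, which share no term. The phrase base state labels the questionnaires in that same sentence, so the variation could be meant relative to the questionnaire-measured state. Part 2 correlates EVEA variations with external scales and describes this as what was done in Part 1. All of this stands, and it is why the point is an inconsistency to reconcile and not a demonstrated faulty analysis. It does not make the text safe, because the method sentence follows directly on the dependence between base level and variation.

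A reader might infer three stronger things.
- That the coupling carries into Part 2. The documents do not support this, because Part 2 names external scales.
- That a spurious finding is bound to appear. It is a raised probability that depends on measurement error and falls as true change varies more between subjects. Sessions 1 and 2 are designed to shift mood, so substantial variation in true change is plausible and the highest rates may not apply.
- That the plan promises a significant dependence here. That wording belongs to the Part 2 music comparison; the Part 1 correlation is only to be explored.

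**Conclusion.** The point holds as a contradiction within Section 4.2: the operands named and the dependence tested are different pairs. On the questionnaire reading, which the Part 2 wording supports, the error rate is nominal. On the literal reading, with variation taken as final minus initial EVEA, the Pearson test at n = 36 has a false-positive rate of about 26% to 89% for reliability 0.9 down to 0.5 with constant true change. It falls to 31% at reliability 0.8 with change SD 0.5, and to 8% at reliability 0.9 with change SD 1. These figures rest on assumed reliabilities, normal scores and true change independent of true mood.

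Severity is minor. The analysis is exploratory, and in Section 4.2 it decides neither the choice of physiological variables nor the music comparison.

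**What to change.** In Section 4.2, state that initial EVEA and EVEA change are each correlated with the base-state questionnaires, in line with the Part 2 wording, and that base EVEA is not correlated with its own change against a null of zero. Define EVEA change in the same sentence.

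If dependence on starting mood is really wanted, name a method that allows for measurement error in the initial score. Change against the mean of the two scores, or a comparison of variances, should not be adopted as a routine replacement: each is valid only if true change does not vary between subjects in a way that raises the final variance.

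The cost is a sentence or two of wording and no new data. The price is that an apparently strong correlation may no longer be reported.

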## 3. Materials and Methods

### 3.1. Design of the Study

The first part of the study will be descriptive and observational where the choice of those parameters (dependent variables) that adequately characterize the emotional state of the subjects will be sought. The second part of the study will be analytical, where the influence of music on changes in the selected dependent variables will be determined. In this second part, a single case study will be made, type AB, for each subject, where in condition A the rehabilitation exercise is carried out in silence, while in condition B it is accompanied by motivating music.

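### The group test of music on EVEA is unpaired and takes no covariate, so the initial EVEA score is at most subtracted; a paired, baseline-adjusted analysis would usually be more precise

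*Protocol article*

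**What the plan says.** Section 3.3.1 of the protocol article says of EVEA: "This scale will be used at the beginning of the data recording once the sensors have been placed and at the end of recording time". Section 3.3.3 gives every session the same format, with an EVEA before and after a main activity of at most 15 minutes, and explains the purpose: "Both baselines allow for the detection of the measurement differentials in each session".

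The second part is a within-person comparison. Section 3.1 states that "a single case study will be made, type AB, for each subject", with exercise in silence as condition A (session 3) and exercise with music as condition B (session 4).

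For the group result, Section 4.2 says "we will analyze the variation in EVEA for sessions 3 and 4 to determine if there is a significant dependence" on music, and continues: "We will use the Kruskal–Wallis test". It names no adjusted analysis of this contrast. The starting level of EVEA appears elsewhere in Section 4.2 only in a correlation analysis, which looks for a dependency "between the base level of EVEA and its variation with respect to the base state".

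**The concern.** Two features of the planned test discard information that the trial will already hold.

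First, Kruskal–Wallis is a rank test for independent groups, but the same people supply both sets of values. Second, it takes no covariate. If the variation is final minus initial, the initial score enters with its coefficient fixed at 1. The best coefficient is the slope of final on initial score within a person, and with equal variances that slope is r. Once stable differences between people are removed, only day-to-day mood links the two readings, and the activity between them is meant to change mood. A slope well below 1 is therefore plausible.

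What is at stake is the chance of detecting a music effect on EVEA with 36 to 40 subjects. The sample size was not derived from this comparison, so the article shows no power margin.

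**Working it through.** **The plan's own figure.** Section 4.1 uses p = q = 0.5, 95% confidence, a 15% margin and a population of 200. Cochran's formula gives 1.96² × 0.25 / 0.15² = 42.68. The finite-population correction gives 42.68 / (1 + 41.68/200) = 35.32, rounded up to 36. The stated 36 reproduces (Section 3.2 plans 40). It rests on estimating a proportion, not on EVEA or on power for music.

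**Inputs.** From the article: n = 36, initial and final EVEA in sessions 3 and 4, and each person in both conditions. "The significance of the tests will be set at three levels", and sidedness is not stated, so two-sided 0.05 is assumed. Also assumed, because the article gives none of them: r, the effect size, equal initial and final variances, and normal data.

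**Variance.** For each person let D0 be the difference in initial EVEA and D1 the difference in final EVEA, both session 4 minus session 3. Each has variance σ² and their correlation is r.
- Paired change score, D1 − D0: variance 2σ²(1 − r).
- D1 adjusted for D0: residual variance σ²(1 − r²).
- Ratio, adjusted to change: (1 − r²) / [2(1 − r)] = (1 + r)/2.

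Estimating the slope has a cost. The variance of the intercept at D0 = 0 is inflated on average by 1 + 1/(n − 3) = 1 + 1/33 = 1.030, and one degree of freedom is spent.

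**Power.** A paired t-test on the change score with 35 degrees of freedom has 80% power at a standardised effect d = 0.480. The adjusted effect is d / √[1.030 × (1 + r)/2], tested on 34 degrees of freedom with noncentrality √36 = 6 times that effect.

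| r | (1 + r)/2 | × 1.030 | adjusted effect | power |
|---|---|---|---|---|
| 0.3 | 0.65 | 0.670 | 0.587 | 92.8% |
| 0.5 | 0.75 | 0.773 | 0.546 | 89.0% |
| 0.7 | 0.85 | 0.876 | 0.513 | 84.9% |
| 0.8 | 0.90 | 0.927 | 0.499 | 82.8% |
| 0.95 | 0.975 | 1.005 | 0.479 | 79.8% |

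Direct simulation of the intercept test (40,000 runs per row) gave 92.5%, 89.1%, 84.9%, 82.9% and 79.7%. In variance terms, break-even is where 1.030 × (1 + r)/2 = 1, that is r = 2 × 33/34 − 1 = 0.94.

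**The test actually named.** A second simulation compared Kruskal–Wallis on the change score with the adjusted paired analysis (36 subjects, 3,000 runs per setting, music effect 0.5 SD of a single score). The settings also differ in how much variance lies between people, so each row should be read across only.

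| r | Kruskal–Wallis, changes uncorrelated across sessions | adjusted | Kruskal–Wallis, changes correlated | adjusted |
|---|---|---|---|---|
| 0 | 0.53 | 0.82 | 0.43 | 0.82 |
| 0.29 | 0.54 | 0.72 | 0.42 | 0.73 |
| 0.5 | 0.73 | 0.84 | 0.59 | 0.85 |
| 0.6 | 0.90 | 0.94 | 0.73 | 0.95 |

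The correlated columns add a subject-level change component with variance 0.3. With no music effect, Kruskal–Wallis then rejected in only 1.1% to 2.9% of runs. The adjusted test rejected in 4.4% to 5.6% across all settings.

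**The case against.** The strongest case against is that analysing change is a valid and common choice, that the article contains no contradiction or wrong figure here, and that covariate adjustment is often left to an analysis plan. The first two parts stand: this is an efficiency point. The third does not dispose of it, because the article itself names a test that excludes both pairing and adjustment.

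Several further objections stand and limit the point.
- The article never defines the variation in EVEA. Within-session change is the natural reading of Section 3.3.3. If final scores were compared instead, the initial score would not be used at all, and the conclusion that it is not adjusted for would still hold.
- The 80% reference is a paired change-score test, which the article does not plan. It isolates the gain from adjustment; the loss from ignoring pairing comes on top when changes correlate across sessions.
- A reader might infer that for r below 0.5 it would be better to drop the initial score. That holds only for paired final scores. Under the planned unpaired test, subtraction is the one step that removes stable differences between people.
- A reader might infer that the change score can never do better. At r = 0.95 and n = 36 it does, by a hair (80% against 79.8%), because the slope must be estimated.
- Unusual starting moods add noise that the variance ratio already counts. They are not a separate bias unless starting mood differs systematically between the two sessions.
- EVEA is a supporting tool in Section 3.3.3. It comes first in the analysis of the second part by sequence; the article does not call it primary.

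**Conclusion.** The point holds as a minor, low-cost improvement. As named, the group EVEA test ignores the pairing and cannot adjust for the initial score. Relative to a paired change-score test with 80% power at 36 subjects, adjustment gains about 13 points at r = 0.3, 9 at 0.5, 5 at 0.7 and 2 to 3 at 0.8, and nothing near 0.95. These sizes rest on an assumed r, an assumed starting power, equal variances and normal data. With two ratings so close in time, a high r and a negligible gain cannot be excluded.

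The documents do not support calling the planned test invalid: in simulation it kept its error rate when changes were uncorrelated across sessions and became conservative when they were correlated. Nor do they support the inference that adjustment would protect the music comparison from order effects. Section 3.3.3 states counterbalancing only for sessions 1 and 2. If starting mood differs systematically between sessions 3 and 4, the change-score and adjusted estimates can differ in value, and neither separates music from order.

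**What to change.** In Section 4.2, define the variation in EVEA explicitly and replace the group Kruskal–Wallis test for EVEA with a paired analysis. The outcome is each person's final EVEA in session 4 minus that in session 3; the covariate is the same difference in initial EVEA; the test of music is the test of the intercept, at zero initial difference. If the authors wish to avoid assuming normality, a sign-flip permutation or rank version of this model serves. Keep the raw within-session change as a descriptive summary.

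No new data or visits are needed. The change replaces the planned test rather than adding a covariate to it, spends one degree of freedom (with a cost of about one point of power, already counted above), and gives an estimate slightly less direct to read than a raw change.

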## 4. Statistical Methodology

### 4.1. Sample Size

The population of the centers is approximately 200 individuals (100 from each center, adults and children). According to Cochran’s formula for estimating the sample, assuming, in the worst-case scenario, a value of *p* = *q* = 0.5 (maximum variance), a confidence interval of 95% and a margin of error of 15%, the sample size would be 36 individuals. Therefore, a sample size with 18 adults and 18 children seems adequate.

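### Section 4.2 compares silence and music in the same subjects by Kruskal–Wallis, an independent-samples test, which is typically conservative here and can cost power

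*Protocol article*

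**What the plan says.** Section 3.1 of the protocol article describes the second part as a within-subject comparison: "a single case study will be made, type AB, for each subject". The conditions are defined there too: "in condition A the rehabilitation exercise is carried out in silence, while in condition B it is accompanied by motivating music". Section 3.3.3 assigns silence to session 3 and music to session 4, and schedules both for the same participant within a two-week programme: "the third and fourth sessions will be set for the second one".

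Section 4.2 then sets the group-level analysis. For mood, "we will analyze the variation in EVEA for sessions 3 and 4", and the test and its justification follow: "We will use the Kruskal–Wallis test, which does not require any type of assumption regarding the normality and homoscedasticity of the samples". For the physiological variables and the average kinetic energy, A and B are compared "by means of a Kruskal–Wallis test applied to the group of subjects, but also at the individual level by means of a permutation test".

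Thresholds of 0.05, 0.01 and 0.001 are attached to these tests. No paired group-level test is named anywhere, and no between-session correlation, effect size or power is given for the music comparison.

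**The concern.** Each subject contributes one member of each pair, so the A and B samples are not independent. Kruskal–Wallis takes its reference distribution from independent groups. The article defends the choice by the assumptions the test avoids (normality, equal variances) and is silent on the one this design breaks.

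Whether music motivates physical activity is one of the two research objectives in the Abstract. The Kruskal–Wallis tests are the only group-level tests of it, for every outcome. If a subject's two sessions are positively correlated, an unpaired test keeps stable differences between people in its error term. Section 3.2.1 admits ages 2 to 65, and Section 3.3.3 fits the exercise to each volunteer's capabilities, so for some measures those differences could be large.

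**Working it through.** **The plan's own figure.** Section 4.1 states that "the sample size would be 36 individuals". With z = 1.96, p = q = 0.5, margin 0.15 and a population of 200:
- n0 = 1.96² × 0.25 / 0.15² = 42.68
- 42.68 / (1 + 41.68/200) = 35.32, rounded up to 36

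The figure reproduces. It is a precision calculation for a proportion, so it says nothing about the power of the A/B comparison.

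**The test.** With two groups of n and N = 2n, H = 12/(N(N+1)) × (R_A²/n + R_B²/n) − 3(N+1), referred to chi-squared on 1 df. This is the squared unpaired rank-sum statistic. If a subject's two values correlate at rho, the variance of the A–B contrast is roughly (1 − rho) times what the test assumes. The actual two-sided error is then about 2 × [1 − Φ(1.96/√(1 − rho))]:
- rho 0.3: 1.9%
- rho 0.5: 0.56%
- rho 0.7: 0.03%

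**Simulation.** The inputs were n = 36 (Section 4.1), one value per subject per session, bivariate normal data, nominal two-sided 5% and 20,000 runs per cell. The correlation rho and the shift d (in SDs of a single session) are assumptions. KW is Kruskal–Wallis and WSR is Wilcoxon signed-rank.

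| rho | Type I error, KW | Power d = 0.5, KW vs WSR | Power d = 0.3, KW vs WSR |
|---|---|---|---|
| 0 | 4.5% | 53% vs 53% | 23% vs 23% |
| 0.3 | 2.0% | 53% vs 67% | 19% vs 30% |
| 0.5 | 0.8% | 54% vs 81% | 15% vs 40% |
| 0.7 | 0.1% | 57% vs 96% | 11% vs 60% |
| 0.8 | 0.01% | 58% vs 99% | 8% vs 77% |

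The signed-rank type I error stays between 4.7% and 5.2% throughout. With n = 40, the number in Section 3.2, the pattern is the same (at rho 0.5 and d = 0.5, 60% vs 85%). A negative correlation would reverse the direction: at rho = −0.3 and n = 36 the KW type I error is 8.1%.

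**Sample size equivalent.** By normal approximation, 80% power at d = 0.5 needs 2 × (1 − rho) × ((1.96 + 0.84)/0.5)² pairs: 63 at rho 0, 44 at 0.3, 32 at 0.5 and 19 at 0.7. Treated as independent samples, it needs 63 per condition.

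**Where EVEA falls.** EVEA is recorded at the start and end of each session and its variation is analysed. If a subject's scores share only a stable level S plus independent noise, the covariance of the two changes is S-variance × (1 − 1 − 1 + 1) = 0. A simulation of this case gave a correlation of −0.004. EVEA could therefore sit near the top row of the table. It would move down if subjects also differ consistently in how much their mood changes.

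**If windows were pooled.** Section 4.2 mentions data windows for the session 1 versus 2 comparison and does not say that they enter the group A/B test. With m windows per subject and session, the ratio of true to assumed variance is (m·σ²_int + σ²_e)/(σ²_b + σ²_int + σ²_e). Here b is between-subject, int is subject-by-session and e is residual. The ratio exceeds 1 only if (m − 1)·σ²_int > σ²_b. Simulations with n = 36, m = 10 and total variance 1 gave:
- σ²_b = 0.7 and σ²_int = 0, 0.02 or 0.05: type I error 0.3%, 0.9% and 3.4%
- σ²_b = 0.5 and σ²_int = 0.2: type I error 19%

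**The case against.** The best defence has four parts.

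- **The error is mostly in the safe direction.** With one value per subject and positive correlation, a significant Kruskal–Wallis result is not undermined. This stands. A reader might infer that the test would produce false music effects, but the documents do not support that in general. It needs a negative correlation, or pooled windows with a sizeable subject-by-session component, and the plan states neither.

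- **The loss may be small for EVEA.** This also stands, because the outcome is a within-session change. For the physiological variables and kinetic energy, the wording leaves open whether a within-session change or the A–B difference is meant. The larger losses apply to measures whose level differs stably between people.

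- **Individual-level permutation tests are planned as well, in keeping with a single-case design.** They do not supply a valid group-level test, and for the A/B comparison they are not planned for EVEA.

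- **An article condenses a fuller plan.** That would excuse an omission. Here a specific test is named twice and justified in the text.

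Two stronger readings are tempting. One is that most of the power of the within-subject design is lost. In the table the relative loss at d = 0.5 is nil at rho 0, (67 − 53)/67 = 21% at 0.3, (81 − 54)/81 = 33% at 0.5 and (96 − 57)/96 = 41% at 0.7. It passes half only for the smaller shift at rho of about 0.5 or more, for example (40 − 15)/40 = 63%. The other is that a real effect is likely to be missed. That too depends on a correlation and an effect size that the article does not give.

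**Conclusion.** The point holds as a wrongly chosen method: an independent-samples test is specified for paired data at every group-level A/B comparison, with a justification that omits the assumption at issue. Its p-values are correctly calibrated only if the two sessions are uncorrelated.

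With one value per subject per session and a correlation between 0 and 0.8, the test ranges from essentially nominal to extremely conservative. The power cost for a 0.5 SD shift ranges from nothing to about 40 percentage points. These sizes rest on assumed correlations and shifts and on normal data; the direction for positive correlation does not depend on the exact values. If windows were pooled, the direction would depend on the variance components.

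**What to change.** In Section 4.2, at both places, replace Kruskal–Wallis by a paired group-level test on one pre-defined summary value per subject per session. Either the Wilcoxon signed-rank test or a sign-flip permutation test of the B − A difference would serve. Report the paired difference with a 95% confidence interval that matches the test, for example the Hodges–Lehmann estimate and interval with the signed-rank test. Delete the sentence that justifies Kruskal–Wallis. Using one summary value per subject also settles the pooled-windows question.

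The cost is a few lines of wording, with no new data or visits. One limit should be stated alongside it. Section 3.3.3 reverses the order for half the participants in sessions 1 and 2 but states no reversal for sessions 3 and 4. A paired test does not separate music from session order and, being more sensitive, would also pick up an order effect more readily. That is a separate point and no reason to keep the unpaired test.
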